# Functional rehabilitation of upper limb apraxia in poststroke patients: study protocol for a randomized controlled trial

**DOI:** 10.1186/s13063-015-1034-1

**Published:** 2015-11-05

**Keywords:** Apraxia, Stroke, Rehabilitation

## Abstract

**Background:**

Upper limb apraxia is a common disorder associated with stroke that can reduce patients’ independence levels in activities of daily living and increase levels of disability. Traditional rehabilitation programs designed to promote the recovery of upper limb function have mainly focused on restorative or compensatory approaches. However, no previous studies have been completed that evaluate a combined intervention method approach, where patients concurrently receive cognitive training and learn compensatory strategies for enhancing daily living activities.

**Methods/Design:**

This study will use a two-arm, assessor-blinded, parallel, randomized controlled trial design, involving 40 patients who present a left- or right-sided unilateral vascular lesion poststroke and a clinical diagnosis of upper limb apraxia. Participants will be randomized to either a combined functional rehabilitation or a traditional health education group. The experimental group will receive an 8-week combined functional program at home, including physical and occupational therapy focused on restorative and compensatory techniques for upper limb apraxia, 3 days per week in 30-min intervention periods. The control group will receive a conventional health education program once a month over 8 weeks, based on improving awareness of physical and functional limitations and facilitating the adaptation of patients to the home. Study outcomes will be assessed immediately postintervention and at the 2-month follow-up. The primary outcome measure will be basic activities of daily living skills as assessed with the Barthel Index. Secondary outcome measures will include the following: 1) the Lawton and Brody Instrumental Activities of Daily Living Scale, 2) the Observation and Scoring of ADL-Activities, 3) the De Renzi Test for Ideational Apraxia, 4) the De Renzi Test for Ideomotor Apraxia, 5) Recognition of Gestures, 6) the Test of Upper Limb Apraxia (TULIA), and 7) the Quality of Life Scale For Stroke (ECVI-38).

**Discussion:**

This trial is expected to clarify the effectiveness of a combined functional rehabilitation approach compared to a conservative intervention for improving upper limb movement and function in poststroke patients.

**Trial registration:**

Clinical Trial Gov number NCT02199093. The protocol registration was received 23 July 2014. Participant enrollment began on 1 May 2014. The trial is expected to be completed in March 2016.

**Electronic supplementary material:**

The online version of this article (doi:10.1186/s13063-015-1034-1) contains supplementary material, which is available to authorized users.

## Background

Apraxia is considered the inability to carry out learned skilled motor acts despite the motor and sensory systems being intact with respect to coordination, comprehension, and cooperation [1, 2]. Specifically, this disorder is viewed as any motor ability problem acquired in the absence of motor impairments, such as weakness, akinesia, loss of sensory input, abnormal tone or posture, or movement disorder [3], which occurs as the result of a neurological dysfunction [4].

Apraxic impairments are classified as higher motor deficits since they may manifest in the absence of primary sensory and motor deficits, disturbed communication or lack of motivation. As the disorder appears when patients are processing goal-directed actions [5, 6], it has been characterized as a reduction in the patient’s ability to voluntarily perform goal-directed movements [7].

Limb apraxia (LA) is a subtype of apraxia covering a wide spectrum of higher motor disorders caused by acquired brain disease or injury and affecting the performance of skilled learned movements carried out by the upper limbs [8]. It cannot be explained by intellectual deterioration, poor comprehension, uncooperativeness or a deficit in the elemental motor or sensory system [9]. Frequently observed clinical symptoms of LA are an inability to perform purposeful movements with one’s arms or hands, errors when asked to demonstrate how to use an object or how to carry out actions involving a single or series of components of movements, and problems imitating abstract and symbolic gestures [5, 10]. Thus, with LA, performance is characterized by a series of errors leading to an incomplete, inaccurate or incorrect gesture [5, 10].

Limb apraxia subtypes are based on the classification of Hugo Liepmann [11]. The subtypes of this syndrome are usually multimodal because they do not depend on the modality of perceptual visual, verbal, or tactile stimuli that the person receives [12]. The two subtypes of apraxia that have been described in the most detail in scientific literature are ideational apraxia (IA) and ideomotor apraxia (IMA). IA occurs when patients have problems performing a sequence of actions requiring the use of various objects in the correct manner and order necessary to complete an intended goal. IMA is the inability to properly perform gesture pantomimes and imitations, whereas the use of real tools is less affected. Patients that present with IMA know cognitively what to do but do not know how to execute the movement. The idea or plan for the action is not damaged, but implementation of the motor plan for turning gestures into actions is impaired [12].

The deficits linked to apraxia are typically associated with brain damage of vascular etiology, especially after left hemispheric stroke [13–15]. Studies report prevalence rates varying from 10 % to 50 % for the traditional clinical classification of IA and IMA deficits after lesions in the left parietal and premotor cortical areas [6, 14, 15]. Patients with right-brain damage and IMA have also been reported, with prevalence rates from 20 % to 54 % [16, 17].

Apraxia is therefore one of the common cognitive deficits that occur after a stroke. It can have negative impacts on a patient’s independence in activities of daily living (ADLs) [14] due to reduced levels of patient autonomy [18–20]. The disorder not only appears in clinical settings but also in many natural, day-to-day environments [10] where patients commonly perform ADLs, that is, the daily activities required to live safely and independently at home. The ecological relevance of apraxia has been reported in the ability of patients to perform various ADLs, for example, feeding, bathing, toileting, and grooming, as well as dressing and brushing one’s teeth. Moreover, gesture deficits impact negatively on patients’ nonverbal communication and the quality of communicative gestures. For this reason, patients who have apraxia rarely use spontaneous communicative gestures in daily living settings [5, 19–24].

To promote the independence and safety of apraxia patients’ daily functional performance, efficient cost-effective and evidence-based intervention strategies for LA are needed. The most important interventions reported in the scientific literature that are currently used for upper limb apraxia can be divided into two approaches: restorative and compensatory. With the restorative method, damaged systems/processes are treated directly, the objective being to bring the partially affected abilities back to their functional level prior to illness. It focuses on the training of transitive and intransitive gestures, with the aim of restoring the patient’s pre-morbid level of function. ADL training is most successful where patients have practiced the activities during their daily routines in natural everyday environments. This gesture execution treatment regimen was developed by Smania and collaborators [6, 10, 25].

Compensatory methods are based on providing strategies for patients to compensate for deficits associated with apraxia. By definition, a compensatory treatment does not lead to the recovery of specific abilities but requires the damaged system to generate compensatory mechanisms. This approach was developed, with specific training strategies, by the Dutch group of Van Heugten and collaborators [6, 12, 26, 27].

Previous studies have reported that rehabilitative treatment of the cognitive functioning of patients with LA after a stroke can bring about significant improvements in the performance and recognition of both transitive and intransitive gestures. Regaining praxis skills often generalizes to improvements in ADL functioning as well. Furthermore, follow-up evaluations indicate that it could have long-term treatment benefits [10, 25].

Evidence of the effectiveness of compensatory strategies through ADL training has also been found in this client group. Results after an eight-week treatment period indicate that integrating specific strategy training into the usual occupational therapy was more effective in improving ADL functioning than usual occupational therapy alone [14]. The results of a similar strategy training approach demonstrated clinically large and statistically significant impacts on all measures of ADL functioning, although small significant improvements were found in tests on apraxia and motor functioning. In the same study, 71 % of the patients had improved Barthel Index scores. These results suggest that the training appears to be successful in teaching patients compensatory strategies that enable them to function more independently, despite the residual impacts of apraxia [26]. However, as this study did not include a control group, these findings could have been affected by other factors. Although previous research has shown that the effective management and treatment of LA has the potential to have a marked impact on patient outcomes, more rigorous empirical evidence is needed to demonstrate the effectiveness of rehabilitation approaches for upper limb apraxia [10]. Only a few studies have been published that have a suitably rigorous study design and a sufficiently large sample size. Also, the efficacy of different apraxia treatments has only been investigated in a few randomized controlled studies [5].

There is some debate as to whether teaching compensatory strategies reduces the likelihood that restorative approaches will be successful because, once learned, compensation is very difficult to modify; that is, it may be difficult to unlearn compensated movement, and this may frustrate any efforts to improve movement with restorative strategies [28, 29]. However, other authors claim that teaching compensatory and restorative frameworks should be combined to determine whether this is in fact true or whether, on the contrary, greater positive effects are achieved with a combined approach.

To our knowledge, no studies have been completed using a combined intervention approach, where patients receive cognitive training on apraxia in conjunction with a method that focuses on the strategies needed to promote ADL functional performance. Moreover, we are not aware of any studies that incorporate an apraxia intervention at home, in other words, in a natural day-to-day context. Hence, a more rigorously designed large scale randomized trial is needed to evaluate the effectiveness of a combined treatment approach to functional rehabilitation at home that integrates both intervention approaches to LA function (restorative and compensatory) with autonomy in ADLs and quality of life (QoL) in poststroke patients.

For these reasons, the overall objective of this randomized control trial is to evaluate the immediate and medium-term effects of a combined functional rehabilitation intervention aimed at improving mild to moderate upper limb apraxia in poststroke patients, using a combination of restorative and compensatory approaches in the patients’ home environments, in comparison with a control group who undergo a traditional health education protocol. The specific research aims are (a) to investigate the impact of a combined functional rehabilitation intervention approach on the independence of patients presenting with an upper limb apraxia that affects the performance of their basic/instrumental activities of daily living, (b) to compare the neuropsychological functional status of patients’ LA, and (c) to assess the impact of this combined intervention in upper limb apraxia on the patient’s quality of life.

Our study hypothesis is that changes induced by the restorative approach in combination with the compensatory approach could have positive effects on the performance of transitive/intransitive gestures, ADLs and QoL in patients with upper limb apraxia.

## Methods/Design

### Research design

This study will be conducted as a two-arm patient and therapist-blinded, parallel, randomized controlled trial design, following the recommendations of the SPIRIT guidelines (Additional file 1) [30]. The experimental group will receive a combined functional rehabilitation program at home and will be compared to a control group receiving a conventional health education program. The main outcome measures will be collected at three time points over a 16-week period: (1) at baseline, (2) at posttreatment (that is, 8 weeks after baseline), and (3) at follow-up (16 weeks after baseline). The study assessment schedule is shown in Table 1. The study was approved on 26 May 2014 by the Investigation Ethics Committee of Granada province-CEI (Andalusian Health Service, Granada, Spain, 180SP) and complies with the 2013 modification of the Helsinki Declaration [31] and with current Spanish legislation for clinical trials [32].

**Table 1 Tab1:** Schedule of enrollment, interventions, and assessments of the study

	Enrollment	Allocation	Post-allocation		
Time point	Pre-treatment	Time 0	Baseline	8-weeks posttreatment	2-month follow-up
Enrollment:					
Eligibility screen	X				
Informed consent	X				
Allocation		X			
Interventions:					
Combined functional rehabilitation of apraxia group			X	X	
Traditional health educative protocol group			X	X	
Assessments:					
Sociodemographic and clinical data			X		
Barthel index			X	X	X
Instrumental Activities of Daily Living Scale			X	X	X
Observation and scoring of ADL-Activities			X	X	X
De Renzi Test for ideational apraxia			X	X	X
De Renzi Test for ideomotor apraxia			X	X	X
Recognition of gestures			X	X	X
Test of upper limb apraxia (TULIA)			X	X	X
Quality of life scale for stroke (ECVI-38)			X	X	X

### Participants

Forty patients with clinical evidence of left and right-sided unilateral vascular lesions poststroke and upper limb apraxia will be recruited from the Neurology Unit of San Cecilio Hospital in Granada, Spain. Initial contact with the patients will be made by telephone 2 months after they sustained the stroke. Participants will be asked to talk face-to-face with the coordinators to discuss the study and obtain information regarding the objectives and characteristics of the research. Those who give their voluntary consent for participating in the study will be interviewed and assessed by a neurologist to determine whether they meet the study inclusion criteria. Written informed consent will then be obtained from all those taking part in the study. Figure 1 shows the flow diagram of the study participants.

**Fig. 1 Fig1:**
[figure not shown]
Flow diagram of study design

### Eligibility criteria

The criteria for inclusion in the study will be as follows: (a) age between 25 and 95 years; (b) presenting with mild to moderate effects of a stroke 2 months after a cerebrovascular attack (this will be determined from a neurological examination and completion of the NIH stroke scale [33, 34]; (c) the presence of upper limb apraxia lasting at least 2 months; (d) voluntary participation; (e) intervention judged to be necessary by the neurologist, occupational therapist. and patient; and (f) patients presenting with apraxia, determined by a score of less than or equal to nine points on the validated tool for apraxia screening (Apraxia screen TULIA) [35].

The exclusion criteria have been established as follows: (a) a history of apraxia predating the current stroke; (b) having had a stroke less than 2 months or more than 24 months previously; (c) cognitive impairment (<23 points in the normal school population and <20 points with a low level of education or illiteracy, in accordance with the Spanish version of the Mini-Mental State Examination) [36]; (d) severe aphasia (when the patients do not understand the commands or are unable to complete the screening tests); (e) a previous brain tumor; (f) a previous history of other neurological disorders; (g) having a mother tongue other than Spanish; (h) a history of known drug addiction; (i) a known intellectual or learning disorder; (j) brain damage from a traumatic or neurodegenerative process (k) a history of serious impairment of awareness; (l) the presence of orthopedic or other disabling conditions; and (m) the patient withholding consent to take part in the study.

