### Randomization and blinding

The patients who volunteer to take part in the study will be randomly allocated into two groups (the experimental and control groups), using a computational random number generator (EPIDAT 3.1, Xunta de Galicia) with randomization codes created by [name]. This will assign patients to a combined functional apraxia rehabilitation group or a control group with an allocation ratio (1:1). During the randomization process, patients will be blinded to their treatment allocation. The neurologist will examine the patients for eligibility criteria and collect all the baseline demographic variables but will not be involved in the rest of the study or preparation of the randomization codes. Treatment allocation will be concealed and patients and study personnel will be blinded to the treatment assignments until after the database has been locked. During the trial, all the outcome measures will be collected by three therapists, who will be blinded to the group allocation. Treatment interventions will all be carried out by an occupational therapist with wide clinical experience, who will be blinded to the outcome measures and baseline examination findings but not to the patients’ treatment allocation, although this allocation will not be revealed to the therapists who gather the outcome measure data. Criteria for receiving discontinued intervention will be as follows: 1) the participant requests voluntarily to miss any session, or 2) the interventions produce a significant improvement or worsening of apraxia disease. As part of the strategy to improve adherence to intervention, patients will be informed about the relevance of the treatment in each session, and they will be telephoned weekly to remind the date of the sessions. The final result of the study will be reported to the patients in both groups.

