### Statistical analysis

The data obtained in this study will be analyzed with SPSS software, version 20.0. The reliability of the model and validity of the hypothesis will be checked and the normal distribution of variables, residuals values and homogeneity of the variances will be studied. The normal distribution of variables will be verified by the Kolgomorov-Smirnov test for continuous variables and the Chi-Square Goodness of Fit test for categorical variables. Residuals will be analyzed using the residuals graph to compare observed values against the residuals values, distribution and tendency. Linearity will be examined using bivariate scatter plots of observed residual values against expected values.

Descriptive statistics will be used first to characterize the study group. The outcomes will be reported with the mean and standard deviation of scores at baseline, post-treatment and follow-up time. To evaluate the main effect of the independent variable (interventions) on outcomes and potential time-by-treatment interactions, repeated measures analysis of variance (RM ANOVA) will be conducted. To check for sphericity, the variances of the differences between all combinations of groups of within-subjects factors will be analyzed with the Mauchly test and verified by the local invariant test. Although the Mauchly test is the most widely used, both tests will be performed because some authors have reported that the local invariant test produces fewer Type II errors than the Mauchly test with small sample sizes and a large number of variables. The Levene test will be used to assess the equality of variances at the 0.05 significance level. Post hoc analyses of significant group x time interaction effects will be carried out using the Tukey multiple comparison procedure to examine pairwise comparisons of the groups’ means for all outcome measures and across the three data collection times.

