## Discussion

This study on the functional rehabilitation of upper limb apraxia will analyze the effects on post-stroke patients of an 8-week integrative and innovative intervention program, focused on two different but complementary approaches for improving the functional performance, autonomy and cognitive function of patients presenting with apraxia. The intervention will take place in the context of the patients’ homes, which provide a natural day-to-day living environment for the study participants.

Apraxia rehabilitation has been researched and reported on in the peer-reviewed literature [2, 5, 6, 46], especially with respect to stroke patients [6, 14], and has been shown to be effective in clinical settings immediately after treatment and on for a longer term. LA has an irrefutable impact on patients’ ADL independence. Although spontaneous recovery of upper limb apraxia is common, it typically does not occur in apraxia patients with ADL abilities; hence, an adequate training can enhance independence and accelerate the natural recovery process [19]. Compensatory and restorative approaches have independently been shown to be effective in improving patients’ ADL function [10, 19, 26, 47]. Both frameworks can be joined together to combine the single effects of each approach, resulting in an effective recovery of the patients. In other words, it is expected that a combination of both approaches will produce better functional outcomes and a better overall patient QoL.

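### Time since stroke at entry may span 2 to 24 months, yet the stated model does not use it; adjusting for it is a cheap gain in precision, and the timing passages should be reconciled

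*Protocol article*

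**What the plan says.** Four statements in the protocol article bear on when patients enter.

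- Participants: "Initial contact with the patients will be made by telephone 2 months after they sustained the stroke". A face-to-face discussion, a neurologist's assessment and written consent follow. No interval from contact to baseline is given.
- Eligibility criteria, inclusion (b): "presenting with mild to moderate effects of a stroke 2 months after a cerebrovascular attack".
- Eligibility criteria, inclusion (c): "the presence of upper limb apraxia lasting at least 2 months", with no upper limit.
- Eligibility criteria, exclusion (b): "having had a stroke less than 2 months or more than 24 months previously".

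Randomization and blinding describes 1:1 allocation from a computer random number generator and names no stratification factor. Statistical analysis says that "repeated measures analysis of variance (RM ANOVA) will be conducted" to test the intervention effect and its interaction with time; no covariate is named.

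On natural recovery, the Discussion begins a sentence with "Although spontaneous recovery of upper limb apraxia is common". It then limits this with a clause, hard to interpret, saying that recovery typically does not occur in patients with ADL abilities. It adds that training can speed up natural recovery. No rate of recovery by time since stroke is given.

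**The concern.** Two things are unsettled. First, the text does not show whether the trial enrols patients close to 2 months after stroke or across the whole window. In the first case the 24-month limit has almost no function. In the second, a patient approached at 18 months satisfies exclusion (b) but does not match the contact rule, and inclusion (b), read literally, could be judged only in retrospect. With 16 weeks of follow-up, results could describe patients at roughly 2 to 6 months after stroke, or patients observed as late as about 28 months.

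Second, if entry is spread out, patients still recovering may change more over 16 weeks than patients who are stable, whichever arm they are in. A model with group and time alone leaves that variation in the error term. With 40 patients, the arms can also differ by chance in their mix of earlier and later patients. The stake is precision on the Barthel Index in a trial with little power to spare.

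**Working it through.** **Inputs from Sample size.** Difference 2.44 Barthel points, SD 3.10, two-sided α 0.05, power 80%, 15 per arm, raised to 40 in total.

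**The plan's own figure.** For a two-sample comparison, n per arm = 2(1.96 + 0.842)² × 3.10² / 2.44² = 25.3, so 26 (27 with the t distribution). The stated 15 per arm is not reproduced. It matches a paired t test on one group's change (power 0.81 at n = 15). That is a separate matter, but it sets the baseline here: two-sample t power is 0.55 at 15 per arm and 0.68 at 20 per arm.

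**Chance imbalance in months.** *Assumption:* entry is uniform over 2–24 months.
- SD = 22/√12 = 6.35 months.
- SE of the between-arm difference in means, 20 per arm = 6.35 × √(2/20) = 2.0 months.
- The arms differ by more than 2 months with probability 0.32, and by more than 3 months with probability 0.14.
- If entry is instead skewed early (2 months plus an exponential with mean 5, capped at 24), the SE is 1.5 months and the probability of more than 2 months is 0.18.
- The expected difference is zero in both cases.

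**Effect on the Barthel estimate.** *Assumption:* half the patients are early and gain g extra points spontaneously, in either arm.
- SD of the chance shift = g × √(0.25 × 2/20), which is 0.16 for g = 1 and 0.32 for g = 2.
- For scale, the SE of the treatment difference is 3.10 × √(2/20) = 0.98.
- With exactly 20 early patients among 40, an imbalance of at least 20 percentage points has probability 0.34 and shifts the estimate by 0.2 × 2 = 0.4 when g = 2. An imbalance of at least 30 points has probability 0.11; at 30 points the shift is 0.6.
- In simulation with g = 2 and no treatment effect, the unadjusted test rejected in 5.1% of trials and the mean estimate was 0.00.

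**Effect on power at 20 per arm.** R² is the assumed share of variance in Barthel change due to time since stroke. The documents do not say whether 3.10 already contains this variation, so both cases are shown. Adjusted SD = 3.10 × √(1 − R²); inflated SD = 3.10 / √(1 − R²).

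| R² | SD after adjustment, if 3.10 includes it | Power, adjusted (unadjusted 0.68) | SD unadjusted, if 3.10 excludes it | Power, unadjusted |
|---|---|---|---|---|
| 0.05 | 3.02 | 0.70 | 3.18 | 0.66 |
| 0.10 | 2.94 | 0.73 | 3.27 | 0.63 |
| 0.20 | 2.77 | 0.77 | 3.47 | 0.58 |
| 0.30 | 2.59 | 0.83 | 3.71 | 0.53 |

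A 2-point extra gain in half the patients has variance 0.25 × 2² = 1.0. That is 1.0/9.61 = 10% of 3.10², so it sits near the R² = 0.10 row. Charging one degree of freedom for the covariate changes the adjusted powers by about 0.001.

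If all patients enter near 2 months, R² is close to zero and nothing is gained.

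**The case against.** The strongest case against has four parts.

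*The passages do not contradict each other.* Contact at 2 months is the first telephone call, not enrolment, and exclusion (b) sets outer limits. Contact at 2 months with later entry satisfies both. This stands: a reader might infer a contradiction, but the text supports only a lack of clarity about the spread at baseline.

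*There is no bias.* A reader might infer that natural recovery distorts the treatment effect. With randomisation and a concurrent control it cancels on average, and type I error stays at its nominal level. This stands too. What remains is lost precision, plus whatever imbalance one particular allocation happens to produce. The ordinary standard error already covers that imbalance.

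*The recovery premise is thin.* The Discussion sentence concerns apraxia rather than the Barthel Index, and it carries a qualifier. No passage says that spontaneous change varies with time since stroke, and inclusion (c) already removes patients whose apraxia resolves within 2 months. This stands as a limit on size, so every magnitude here is labelled as an assumption. It does not make equal change across a 22-month window a safe presumption.

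*Covariates and stratification may be settled in a fuller protocol or analysis plan that is not shown.* This is correct, and the absence of a covariate or stratification factor from the article is therefore not treated as an error. The point is an improvement to the model as stated. Other baseline variables could also be argued for; time since stroke is singled out because the article's own entry criteria allow it such a wide range.

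**Conclusion.** The point holds as a modest, low-cost improvement together with a request for clarification. The timing statements are compatible, but they do not fix how widely time since stroke varies at baseline. If it spans most of 2 to 24 months, the model as stated gives up some precision. With half the patients early and 2 extra points of spontaneous gain, the typical chance shift is about 0.3 points against a target of 2.44. With R² of 0.05 to 0.30 inside the SD of 3.10, adjustment lifts power at 20 per arm from 0.68 to 0.70–0.83. If 3.10 excludes this variation, unadjusted power falls to between 0.66 and 0.53.

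The entry distribution, the early share, the extra gain and R² are all assumptions; the documents supply none of them. If entry is concentrated near 2 months, the benefit is negligible. The documents do not support a claim of systematic bias or of a false-positive rate above 5%.

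**What to change.** 1. Reconcile the Participants section with inclusion (b) and exclusion (b). State when after the stroke patients are approached, at what point stroke effects are judged, and how time from stroke to baseline is bounded. This review does not choose the window.
2. Before database lock, pre-specify months since stroke at randomisation as a covariate in the between-arm Barthel comparison at weeks 8 and 16, and fix its scale in advance. Within the repeated measures model it must be allowed to interact with time. A covariate that only shifts a patient's overall level does nothing for the group-by-time test.
3. Report the distribution of time since stroke by arm.

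Allocation need not change, since enrolment began in May 2014. Time since stroke must already be established to apply exclusion (b), so no new data are needed. The cost is a sentence or two in the analysis section and one degree of freedom per comparison, with little return if entry times prove narrow.
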